### Data gathering and analysis

The informed consent form for the T-RAD study includes blood and biopsy sampling, immunological characterization, gene profiling, radiological analysis, and studies of tumor immune cell infiltrate. Blood samples will be collected pre-, during and post-treatment and both PBMCs and plasma will be frozen down. Tumor biopsies will be collected pre- and post-completion of treatment. Patients will sign an informed consent that includes all the above sampling and analyses.

Data on adverse events according to NCI CTCAE v4.0 will be documented as well as vital signs and ECOG performance status. Analysis on samples collected will include hematology and clinical chemistry, tumor markers as well as plasma cytokines measured by BioplexPro™ Human Cytokine 27-plex Assay (Bio-Rad Laboratories Inc.). Assessment of tumor responses will be completed according to the response evaluation criteria in solid tumors (RECIST) 1.1/immune-based therapeutics RECIST based on computed tomography (CT) scans of the thorax, abdomen and pelvis as well as according to the positron emission tomography (PET) response criteria defined by the European Organization for Research and Treatment of Cancer (EORTC)/PET response criteria in solid tumors (PERCIST) (44, 45) using (18)F-fluorodeoxyglucose (FDG) PET scans (46). In addition to conventional measurements the FDG PET evaluation will include metabolic tumor volume (MTV) and total lesion glycolysis (TLG). Such imaging scans will be obtained prior to trial entry to be used as baseline (< 4 weeks of treatment start), at the 3 week mark, at completion of treatment (week 6) and again 6 weeks after treatment completion (week 12) and subsequently every 3^rd^ month until progression, or as per physician’s discretion. Finally, PROMs will be applied through questionnaires pre-, during and post-treatment. For assessment of T cell infiltration into tumor tissue some biopsy specimens will be sent to Veracyte in France (Luminy Biotech Enterprises) for immuno-oncologic diagnostics.

Samples will be collected prior to, during and after treatment. **Table 4** lists the samples and scans that are scheduled.

**Table 4 T4:** Samples to be collected in the T-RAD study.

Tumor biopsies
Collected pre- and post-treatment. Post-biopsies will be obtained within one week of last T cell infusion and again and at 4-6 weeks post treatment completion and/or upon progression.
If sufficient tissue is available, three biopsies will be obtained at each timepoint and prioritized in the following order: 1. FFPE tissue 2. Snap-frozen tumor biopsies 3. Fresh tumor cells/tumor infiltrating lymphocytes prepared into a cell suspension
Blood samples will be collected pre-, during and post-treatment: 1. Peripheral blood mononuclear cells, processed with gradient centrifugation and frozen on liquid nitrogen (up to 10 samples scheduled) 2. Plasma/serum, separated and frozen (up to 17 samples scheduled) 3. Circulating tumor DNA/cells (only if sufficient resources available) 4. FDG PET/CT analysis at baseline (< 4 weeks of the first T cell infusion), again at the 3 week mark, at time of treatment completion (week 6), 6 weeks after treatment completed (week 12) and subsequently every 3^rd^ month or at progression

### Patient reported outcome measures

Participants will be asked to answer Quality of Life Questionnaires (QoL), at the start of the T cell infusions, at the 3 week mark, at the end of the treatment protocol at 6 weeks, at the 12 week follow-up and at the 24 week mark or as per physicians discretion. The questionnaires that will be applied are from the EORTC: Core Quality of Life Questionnaire, QoL-QLQ-C30 version 3.0 and Quality of Life Questionnaire-Lung Cancer 13, QoL-QLQ-LC13 version.

The QoL-QLQ-C30 is designed to assess the health-related quality of life of cancer patients. The questionnaire has 5 functional scales, nine symptom scales and a global health status, allowing for incorporation of physical, psychological, and social functioning into our assessments and refers to the patient’s perception of both the treatment and the illness.

The QoL-QLQ-LC13 is a lung-cancer specific questionnaire to be used in conjunction with the QLQ-C30 and is developed and validated in patients with lung cancer. This questionnaire includes domains of lung-cancer-related symptoms as well as treatment side effects. Both questionnaires will be scored according to the manual provided by EORTC (47).

### Withdrawal criteria

Patients may be withdrawn from the T-RAD study and its assessments at any time. Specific reasons for withdrawal include those seen in **Table 5**.

**Table 5 T5:** Withdrawal criteria for the T-RAD study.

Withdrawal criteria
Voluntary withdrawal by the patient at any time
Safety reasons as determined by the responsible physician
Significant non-compliance to protocol as determined by the responsible physician.
Incorrect enrolment i.e., the patient does not meet the required inclusion/exclusion criteria
Patient is lost to follow-up
A female patient becoming pregnant
Disease progression
Deterioration of the patient’s condition that warrants discontinuation of the study treatment
Related Serious Adverse Event
Non-compliance to trial treatment

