### Objectives and rationale

The primary objective is to evaluate toxicity, safety, and tolerability of the treatment. This will be achieved through monitoring and documentation of incidence, nature and severity of adverse events graded according to National Cancer Institute Common Terminology Criteria for Adverse Events (NCI CTCAE) v4.0. In addition, clinical assessment, including vital signs and Eastern Cooperative Oncology Group (ECOG) performance status, hematology and clinical chemistry and plasma cytokine laboratory results will be monitored.

Secondary objectives are to assess clinical response to the treatment through progression-free survival (PFS) and radiological overall response rate (ORR) as defined by RECIST 1.1/iRECIST for CT scan results and EORTC/PERCIST for FDG PET scan results, see further in section on data gathering and analysis. Additionally, time to progression (TTP) and overall survival (OS) will be evaluated. Finally, patient reported outcome measurements (PROMs) in terms of cancer symptoms and health-related quality of life will be applied in the form of EORTC questionnaires (European Organization for Research and Treatment of Cancer).

Exploratory objectives are assessment of changes in T cell infiltration into tumor tissue, spatial orientation of such changes as well as PD-L1 and PD-1 expression in biopsies pre-treatment and upon progression. See **Table 1** for list of objectives.

**Table 1 T1:** Primary, secondary, and explorative objectives in the T-RAD study.

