### Safety measures and handling of potential toxicities

Administration of autologous Radium-4 T cell immunotherapy has a very good risk-benefit profile. No difference in the nature of the toxicity is to be expected from repeated doses vs a single dose although a stronger response could occur with more numerous doses. The dose regimen applied in the T-RAD trial is comparable to prior studies and the same we applied in our prior clinical study of Radium-1 TCR (ClinicalTrials.gov: NCT03431311, manuscript in preparation) with minimal toxicity (31). Patients enrolled in the T-RAD study will be treated in an inpatient ward and attended to by staff trained to monitor for and respond to emergencies, especially to the development of Cytokine Release Syndrome (CRS) or Tumor Lysis Syndrome (TLS). We have in place special protocols for treatment of both CRS and TLS.

All serious and non-serious adverse events will be monitored and graded according to NCI CTCAE v4.0. Clinical assessment (including vital signs, interim history, physical exam) and laboratory values will be monitored and evaluated prior to each infusion. All adverse events, during the study and for up to 30 days after the last dose, will be documented, reported, and recorded in the patient’s file. Study patients who have an adverse event will be followed until the event has resolved, is determined to be stable, patient withdraws consent or is lost to follow-up or if study treatment is determined to not be the cause of the adverse event. As an additional safety measure, the first two patients will be included with a minimum of 4 weeks between start of treatment. For treatment of adverse events the protocol refers to the Investigator’s Brochure (IB) for this study.

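### The withdrawal rule merges stopping treatment with leaving the study and its assessments, so overall survival can be informatively censored and late questionnaires lost in patients who do badly

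*Protocol article*

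**What the plan says.** The lead sentence of Withdrawal criteria reads "Patients may be withdrawn from the T-RAD study and its assessments at any time". The reasons are in Table 5, a single undivided list. Some entries end participation by their nature: voluntary withdrawal and loss to follow-up. Others are clinical events: "Disease progression", "Related Serious Adverse Event" and "Deterioration of the patient’s condition that warrants discontinuation of the study treatment". The last of these describes stopping treatment, yet it stands as a reason for leaving the study.

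Other sections assume that follow-up continues:

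- Objectives and rationale: "Additionally, time to progression (TTP) and overall survival (OS) will be evaluated". The same section plans biopsies before treatment and at progression.
- Statistical analysis: the clinical response endpoints use Kaplan-Meier methods, all endpoints are to be analysed in all treated patients, and missing data are not imputed unless specified.
- Safety measures: "Study patients who have an adverse event will be followed until the event has resolved", with further exits for a stable event, withdrawn consent, loss to follow-up, or a finding that treatment was not the cause. Events are recorded for up to 30 days after the last dose.
- Table 4: post-treatment biopsies within a week of the last infusion, then at 4-6 weeks after completion and/or upon progression.
- Patient reported outcome measures: questionnaires at the start, at weeks 3 and 6, then "at the 12 week follow-up and at the 24 week mark", or at the physician's discretion.

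**The concern.** Stopping infusions and leaving the study have different consequences for the data. A patient who stops infusions can still contribute a survival time, the outcome of an adverse event and later questionnaires. A patient withdrawn from assessments may contribute none of these.

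Progression and deterioration are expected to be closely linked to death. If patients leave at those events, Kaplan-Meier treats them as having the same later risk of death as those who remain. That assumption is doubtful in metastatic disease with no other treatment option, and the likely error flatters the treatment. A single-arm trial has no control group to expose it, and with 10 patients each one is a tenth of the data. Because withdrawal is permitted and not required, who is followed would also depend on individual judgement. Questionnaire summaries at weeks 12 and 24 could shift towards the patients doing best, since the default is no imputation.

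**Working it through.** **1. The passages side by side.** The plan gives no figure to reproduce on this point; the sample size of 10 has no power calculation behind it.

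- *Survival and analysis set.* Table 5 permits withdrawal from assessments at progression, while Statistical analysis wants every endpoint in every treated patient. Both can be met only if vital status is still collected after withdrawal, which the article does not say.
- *Adverse events.* Progression, deterioration and a related serious adverse event are not among the exits in Safety measures. Table 5 makes each a ground for leaving assessments. The two instructions conflict.
- *Biopsies.* Progression triggers a planned biopsy and also permits withdrawal. The two need reconciling.
- *Questionnaires.* The week 12 and 24 schedule is not conditional on being progression-free, but nothing says that it survives withdrawal.

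**2. Size of the OS bias if every progressor leaves at progression.** All hazards here are assumptions, per month: progression a = 0.25-0.30, death without progression b = 0.02-0.10, death after progression c = 0.10-0.20.

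True survival: S(t) = exp(-(a+b)t) + [a/(a+b-c)] × [exp(-ct) - exp(-(a+b)t)].

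Kaplan-Meier limit with exit at progression: exp(-bt).

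At t = 6 months:

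- (a, b, c) = (0.30, 0.05, 0.20): S = 0.1225 + 2.0 × (0.3012 - 0.1225) = 0.480. Kaplan-Meier gives exp(-0.30) = 0.741. Excess 26 points.
- (0.30, 0.02, 0.20): S = 0.1466 + 2.5 × (0.3012 - 0.1466) = 0.533. Kaplan-Meier gives exp(-0.12) = 0.887. Excess 35 points, the largest in the range.
- b = c = 0.10: both equal exp(-0.60) = 0.549. Excess zero, because progression then carries no extra risk of death.

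Over the whole assumed range the excess runs from 0 to about 35 points.

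**3. What if only some leave?** A separate simulation assumed median progression-free survival of 2, 3 or 4 months, median survival after progression of 3, 5 or 8 months, and 10% or 20% of patients dying without progression. It used 200,000 simulated patients per scenario.

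| Progressors leaving at progression | OS excess at 6 months | OS excess at 12 months | Deaths observed per 10 patients |
|---|---|---|---|
| All | 0.04-0.35 | 0.06-0.53 | 1-2 |
| Half | 0.01-0.10 | 0.00-0.13 | 5.5-6 |

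For example, with medians of 3 and 3 months and 10% dying first, true 6-month OS is 0.56. Kaplan-Meier gives 0.66 if half leave and 0.87 if all leave. The bias was never downward in the scenarios tried, and it was small where survival after progression was long. If vital status is followed after progression, Kaplan-Meier recovers the true curve.

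**The case against.** The strongest reply is that Table 5 is mainly a list of reasons to stop treatment. Its deterioration entry refers to discontinuing study treatment, another entry to non-compliance with trial treatment, and the biopsy plan shows that the authors did not regard progression as an automatic end of assessments. The article is also a condensed account: a fuller protocol may provide survival follow-up and OS censoring rules, whose absence here is no fault.

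Much of this stands. A reader might infer that OS *is* censored at progression. The text does not say so: withdrawal is permissive and no OS censoring rule is given. A reader might also infer that adverse-event follow-up stops after a related serious event, or that biopsies stop at progression. The documents do not support either. Safety measures continues event follow-up past all three clinical reasons, and progression is itself a biopsy time point. What remains there is conflicting instructions, with some risk to newly arising events, the 30-day window and later biopsies if the withdrawal rule were taken to prevail. Late questionnaires would also thin out through death and illness under any wording.

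The reply does not remove the point. The lead sentence expressly extends withdrawal to assessments, and the article states this rule; it is not merely silent. If the full protocol already separates the two decisions, this text needs only to be aligned with it.

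**Conclusion.** The point holds as a defect of wording with statistical consequences. As written, the rule allows OS to be informatively censored at progression or deterioration and allows week 12 and 24 questionnaires to be lost selectively. It also conflicts with the adverse-event and biopsy provisions, which must be reconciled with it.

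No single size can be given. The 0 to about 35 points at 6 months rests on assumed hazards and on every progressor leaving; the 1 to 10 points rests on assumed medians and half leaving. A reader might take a narrower band, such as 14-26 points, from a few chosen hazard combinations, but it does not represent the full assumed range.

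This should be fixed, but it is not critical. OS is one of several secondary endpoints in an exploratory, unpowered, single-arm study, and the specific rule in Safety measures largely protects the primary safety objective.

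**What to change.** Split Table 5 in two:

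1. Reasons for discontinuing study treatment, keeping the clinical list unchanged.
2. Reasons for ending study follow-up, limited to withdrawal of consent or loss to follow-up.

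Reword the lead sentence to match. State that patients who stop treatment remain in follow-up for vital status, adverse events, scheduled questionnaires and already planned samples, as far as they are able and consent. State that OS is not censored at progression or treatment stop. Then reconcile Withdrawal criteria with Objectives and rationale, Safety measures, Table 4 and Patient reported outcome measures.

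The cost is a wording amendment and a few more follow-up contacts in about 10 patients at one hospital. No view is taken on when treatment should stop.

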### Statistical analysis

The primary objective of the T-RAD study is safety. Statistical analysis will be performed after at least one patient has been enrolled, treated, and response has been evaluated. Per protocol, all end points will be analyzed in all treated patients. Safety analysis will include all patients who received treatment. Safety monitoring is the main aim of this trial and thus a power analysis is not applicable beforehand, but the number of patients is similar, to that analyzed in comparable trials (31). The secondary objectives focus on clinical response and are based on PFS, ORR, TTP and OS. For this the Kaplan-Meier methodology will be used. Given the exploratory nature of this phase I study, no adjustments for multiple comparisons will be made.

The samples size is based on clinical considerations and the dose-escalation design. Descriptive statistics include means with standard deviations or medians with minimum and maximum for continuous variables. Counts and percentages will be provided for categorical variables. Missing data will not be imputed unless specified. Confidence intervals will be used where appropriate. All statistics will be done as advised by statisticians.

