**Figure 3 f3:**
[figure not shown]
Flow Diagram for the T-RAD study created using the CONSORT 2010 Flow Diagram.

Patients will receive treatment according to our treatment protocol that includes 12 intravenous infusions, evenly distributed over the course of 6 weeks. Doses are escalating starting at 1 x 10^8^ cells and reaching 2 x 10^9^ cells, see **Figure 4**. Our goal is to treat 10 patients with Radium-4 redirected T cells.

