### T cell manufacture

For T cell manufacturing (see **Figure 1**) we will collect peripheral blood mononuclear cells (PMBCs) from participants by leukapheresis. At the GMP facility of the Department of Cellular Therapy at The Oslo University Hospital, Norway, lymphocytes will be enriched through elutriation (ELUTRA, TerumoBCT) and expanded using CD3/CD28 CTS™ Dynabeads™ (Thermo Fisher Scientific). Lymphocytes will be expanded in CellGro GMP DC medium (CellGenix, GmbH, Germany) supplemented with 5% human serum (PAN-Biotech, GmbH, Germany), Mucomyst (Mylan Healthcare Norway AS), gentamycin (Sanofi Aventis, France) and 100 U/mL interleukin-2 (IL-2) (Proleukin, Clinigen Healthcare Ltd, UK) for 10 days. Expanded T cells will be electroporated and transfected with *in vitro* transcribed (ivt) codon-optimized mRNA (clinical grade, produced at Oslo University Hospital, Norway) encoding the Radium-4 TCR, as previously described (20) and **Figure 5**. Following recovery in medium containing human serum the desired amount of T cells used for injection will be transferred to individual freezing bags, frozen and stored in DMSO-containing cryopreservation media in liquid nitrogen, vapor phase. At the time of infusion, frozen T cells will be thawed at the GMP facility and thereafter immediately transferred to the clinical ward and infused through an intravenous access. Quality-control test criteria will have to be met prior to infusion of the product pertaining to T cell count, viability, and absence of microbiological contamination. See **Table 2** for release criteria for the final cellular product.

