### Participant selection

We intend to treat and fully evaluate 10 patients with metastatic NSCLC > 18 years old of any race or gender with an ECOG score of 0-1 and > 3 months life expectancy. This phase I study will include and treat patients at Oslo University Hospital. HLA-typing will be performed by the National Tissue typing Laboratory. See **Table 3** for selected inclusion and exclusion criteria for the T-RAD clinical study.

**Table 3 T3:** List of selected inclusion and exclusion criteria to be used in the T-RAD clinical study.

Inclusion criteria	Exclusion criteria
Metastatic NSCLC and an HLA-DP*04:01 or HLA-DP*04:02 genotype	Other metastatic malignancies
No other treatment option available	Other anti-tumor treatment < 4 weeks of first T cell infusion in T-RAD
Measurable metastatic disease according to RECIST 1.1/iRECIST	Steroid treatment, except substitution doses
ECOG performance score of 0-1	Significant cardiac or other medical illness that would severely limit activity or survival such as severe congestive heart failure, unstable angina or serious cardiac arrhythmia
Life expectancy of at least 3 months	Active infection requiring antibiotic therapy
Willing to provide blood samples and tissue biopsies for research	Known hypersensitivity to any of the components of the infusion product
Adequate organ function as defined in the treatment protocol	Patients who test positive for hepatitis B, C, HIV or syphilis
Women or men aged ≥ 18 years	Pregnant or breastfeeding
Signed informed consent	Any reason why, in the opinion of the investigator, that the patient should not participate in this clinical trial

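### The stated safety set covers infused patients only, so leukapheresis and trial-biopsy harm in participants who are never infused falls in no stated analysis

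*Protocol article*

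**What the plan says.** The Statistical analysis section gives two population rules. For safety: "Safety analysis will include all patients who received treatment". For everything: "Per protocol, all end points will be analyzed in all treated patients". The same section treats enrolment and treatment as separate steps: "Statistical analysis will be performed after at least one patient has been enrolled, treated, and response has been evaluated".

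Two invasive procedures come before the first infusion:
- **Leukapheresis.** Under T cell manufacture, "we will collect peripheral blood mononuclear cells (PMBCs) from participants by leukapheresis".
- **Tumour biopsies.** Data gathering and analysis schedules them before and after treatment. Table 4 adds: "If sufficient tissue is available, three biopsies will be obtained at each timepoint". Table 3 makes consent to them an entry condition: "Willing to provide blood samples and tissue biopsies for research".

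On recording, the section on safety measures covers "All adverse events, during the study and for up to 30 days after the last dose". It gives the end of the window but not the date or event that opens it.

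**The concern.** Safety is the primary objective, and an autologous product cannot be given without first collecting cells. The biopsies are taken for research. A participant who has a complication of either procedure, and who for whatever reason does not go on to infusion, has been exposed to harm through the trial. Under the stated population rules that participant contributes to no analysis.

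The gap runs in one direction: it can only lower the count of procedure-related harm, never raise it. With about 10 treated patients, a single procedure complication is information that a reader of the results would want to see.

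**Working it through.** The article states no figure on this point to reproduce. The target of 10 treated patients rests on clinical considerations, without a power calculation. The check is therefore first textual, then an illustration on assumed inputs.

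**1. Does treatment mean infusion?** Yes, for three reasons.
- Study design and treatment schedule says: "Patients will receive treatment according to our treatment protocol that includes 12 intravenous infusions".
- The baseline scan window is under 4 weeks before the start of treatment in the text of Data gathering and analysis, and under 4 weeks before the first T cell infusion in Table 4. It is the same scan, so the two starting points are the same.
- Statistical analysis lists enrolled and treated as distinct states.

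**2. Can a participant have the procedures and not be infused?** Yes. After leukapheresis come 10 days of expansion, then electroporation, freezing and quality-control release (T cell manufacture, Table 2), and a threshold of 60% specific killing by 10 hours (T cell potency testing). Table 5 allows withdrawal at any time, with safety reasons, disease progression and deterioration among the grounds. Entry requires a life expectancy of only 3 months or more.

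**3. Does any stated analysis cover such a participant?** None does. Both population rules refer to treated patients, and no other section adds a set.

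**4. Illustration of size.** Two inputs are needed and the article gives neither:
- k, the number who undergo the procedures but are never infused, beside 10 infused. Assumed 1, 3 or 5.
- p, the per-patient risk of a notable procedure event. Assumed 5% or 10%, and the same for every patient.

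Share of exposed participants outside the safety set = k/(10 + k). Chance that at least one event falls outside it = 1 − (1 − p)^k.

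| k | k/(10 + k) | p = 5% | p = 10% |
|---|---|---|---|
| 1 | 1/11 = 9% | 1 − 0.95 = 5% | 1 − 0.90 = 10% |
| 3 | 3/13 = 23% | 1 − 0.95³ = 14% | 1 − 0.90³ = 27% |
| 5 | 5/15 = 33% | 1 − 0.95⁵ = 23% | 1 − 0.90⁵ = 41% |

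If k is zero, nothing is lost. If p is 2%, the figures for k = 1 and k = 5 fall to 2% and 10%.

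**The case against.** The strongest case for the plan is that its safety set matches its objective. Objectives and rationale frames the primary objective as toxicity, safety and tolerability of the treatment. The section on safety measures names two groups of potential toxic effects: cross-reactivity or off-tumour reactivity, and cytokine release or tumour lysis syndrome. All of these come from infused cells, and an uninfused patient cannot show them. A treated-patient set is conventional for that purpose. This stands, and the infused set should stay.

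It can also be said that the safety sentence says who is included without saying that nobody else is. The article condenses a fuller protocol, and the participant flow diagram (Figure 3) is not shown in the text at hand. A listing of pre-infusion events may exist elsewhere. That stands in part: the point is about what the stated rules cover, and it does not show that the sponsor intends to discard these events. Even so, the population is fixed here for safety and again for all end points, so restriction to infused patients is the natural reading.

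A reader might infer more than the article supports, in three ways:
- **That the rule removes events because they were severe enough to stop infusion.** This could happen under Table 5, but nothing says that it will. The barriers described in most detail, release and potency, concern product quality and need not relate to procedure harm. The flat risk in the table does not model such selection.
- **That these events are certainly recorded and then ignored.** The start of the recording window is not stated, so they may be recorded or may not.
- **That one missed event would turn 0/10 into, say, 1/13 for the primary result.** That pools uninfused patients into a rate that should be kept separate. Infusion toxicity of 0/10 would remain 0/10.

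**Conclusion.** The point holds in a limited form. As written, adverse events of leukapheresis and trial biopsies in never-infused participants fall outside every stated analysis, so procedure-related harm could be under-reported. Pre-infusion events in patients who are later infused are not excluded by the population rule. It would be wrong to conclude that the primary safety result is biased: for toxicity of the infused cells, the infused set is appropriate.

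The size cannot be settled from the article. The range of about 5% to 41% for at least one unreported event rests wholly on two assumptions: 1 to 5 never-infused participants, and a 5% to 10% risk common to all. It shows that the gap need not be negligible and is not an estimate for this trial. Priority is minor to moderate: the gap is real and runs one way, and closing it is cheap.

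**What to change.** In Statistical analysis, keep the infused set and add a second, separate summary. Suggested wording:

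*Adverse events after the first infusion are analysed in all patients who received at least one infusion. Adverse events from the first trial procedure up to the first infusion are summarised descriptively, by procedure, in all participants who underwent leukapheresis or a trial biopsy, whether or not they were infused. The number never infused and the reasons are reported.*

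In the section on safety measures, state that adverse-event recording opens at the first trial procedure.

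The cost is one extra descriptive table and, if recording currently opens later, some additional adverse-event recording before infusion. No further patients, visits or procedures are needed. The reported safety profile may look slightly less favourable.

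### Kaplan-Meier is assigned to the overall response rate, which is a proportion of patients and should be analysed as responders over all treated patients

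*Protocol article*

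**What the plan says.** In the Statistical analysis section, the secondary objectives "are based on PFS, ORR, TTP and OS. For this the Kaplan-Meier methodology will be used". No endpoint is excepted.

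Objectives and rationale defines the response endpoint as "radiological overall response rate (ORR) as defined by RECIST 1.1/iRECIST for CT scan results and EORTC/PERCIST for FDG PET scan results". Nothing in the article recasts it as time to response.

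Three other statements bear on the point:

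- The analysis population: "Per protocol, all end points will be analyzed in all treated patients".
- A general descriptive rule: "Counts and percentages will be provided for categorical variables". It is not tied to ORR.
- The planned size: "We intend to treat and fully evaluate 10 patients with metastatic NSCLC".

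Data gathering and analysis schedules imaging at baseline, at weeks 3, 6 and 12, and then every third month until progression or at the physician's discretion. Table 5 lists disease progression among the reasons for withdrawal. The article gives no event or censoring rule for an ORR analysis.

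**The concern.** Kaplan-Meier estimates the distribution of a time to an event. ORR has no time axis: each patient either meets the response criteria or does not, and the rate is a count over a denominator. The method can be used on response only by switching to a different quantity, time to first response. A rule is then needed for patients who progress or stop without responding. Censoring is the obvious candidate here, because progression is a ground for withdrawal and scheduled imaging runs only until progression.

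Censoring treats those patients as though they could still respond later at the same rate as the patients who remain. The risk set at weeks 6 and 12 is then smaller than the number treated, which works against the section's own statement that all endpoints are analysed in all treated patients. With about 10 patients, each one removed moves the estimate visibly. The reported response rate could be too high, with an interval that is not the one for a simple proportion.

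**Working it through.** The article gives no expected response rate, event count or power figure, so there is nothing of its own to reproduce. The check compares the two analyses on illustrative data.

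**Inputs from the article:** 10 treated patients; imaging at weeks 3, 6 and 12.

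**Assumed:** the number and timing of responses and progressions. A non-responder who progresses or stops at a visit is censored there, after that visit's responses are counted.

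**Formulas.** Proportion: x/10. One minus Kaplan-Meier: 1 − Π(1 − d/r), where d is the number of responses and r the number at risk at each visit.

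**Direction.** Kaplan-Meier starts each patient with weight 1/10 and passes the weight of a censored patient to those still at risk. A responder's weight is therefore never below 1/10, and one minus Kaplan-Meier can equal x/10 or exceed it, but cannot fall below it.

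**Two responders (one at week 6, one at week 12), so x/10 = 20%:**

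| Censored at week 3 / week 6 | At risk at week 6 / week 12 | 1 − KM |
|---|---|---|
| 2 / 1 | 8 / 6 | 1 − (7/8)(5/6) = 27.1% |
| 2 / 3 | 8 / 4 | 1 − (7/8)(3/4) = 34.4% |
| 4 / 2 | 6 / 3 | 1 − (5/6)(2/3) = 44.4% |
| 4 / 3 | 6 / 2 | 1 − (5/6)(1/2) = 58.3% |

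**Other timings:**

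- Responses at weeks 3 and 6, with 4 and 2 censored: 1 − (9/10)(4/5) = 28.0% against 20%.
- One response at week 6, with 4 censored at week 3: 1/6 = 16.7% against 10%.
- One response at week 12, with 5 and 2 censored: 1/3 = 33.3% against 10%.

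**Cases with no excess:**

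- Both responses at week 3: 2/10 = 20% by either method.
- No responses: 0% by either method.
- Responses at weeks 6 and 12, with all non-responders kept at risk to week 12: 1 − (9/10)(8/9) = 20%.

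**Average over many trials.** This used 20,000 simulated trials of 10 patients over three visits, with assumed per-visit probabilities for patients still at risk:

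| Response / progression per visit | Mean x/10 | Mean 1 − KM | Excess (points) |
|---|---|---|---|
| 0.05 / 0.20 | 11.5% | 14.2% | 2.7 |
| 0.07 / 0.30 | 14.0% | 19.3% | 5.3 |
| 0.10 / 0.40 | 17.5% | 26.6% | 9.0 (unrounded 26.58 − 17.54) |

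A closed-form check of the first row agrees. The expected proportion is 0.05 × (1 + 0.75 + 0.75²) = 11.6%, and one minus Kaplan-Meier is about 1 − 0.95³ = 14.3%.

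**ORR as a proportion of 10, exact 95% interval.** The lower limit is the 2.5% point of Beta(x, 10 − x + 1) and the upper limit the 97.5% point of Beta(x + 1, 10 − x); for x = 0 the lower limit is 0.

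- 0/10: 0% (0 to 30.8%)
- 1/10: 10% (0.3% to 44.5%)
- 2/10: 20% (2.5% to 55.6%)
- 3/10: 30% (6.7% to 65.2%)

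**The case against.** The best defence is that the sentence is loose drafting of a four-item list. Response is a categorical variable, and the same section promises counts and percentages for categorical variables, all treated patients as the population, and confidence intervals where appropriate. Taken together these already lead to responders over treated patients, and with ten patients anyone can count the responders. That makes a published Kaplan-Meier response rate unlikely. It does not cancel the sentence: the general rule does not mention ORR, while the Kaplan-Meier sentence does. At best the section supports two different analyses of one endpoint.

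It is also fair that the bias needs three steps that the article does not state: recasting ORR as time to first response, censoring at progression or withdrawal, and reporting one minus Kaplan-Meier as the rate. Table 5 and the imaging schedule make the censoring plausible but do not prescribe it. The 58% figure is close to a worst case, because its second response comes when only two patients remain at risk.

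A reader might extend the criticism to TTP and infer that deaths without progression will be censored, so that progression is overstated. The article does not support this. It says only "Additionally, time to progression (TTP) and overall survival (OS) will be evaluated", with no event definition and no rule for deaths. Kaplan-Meier for TTP is not an error in itself, and the definition may properly stand in the full protocol or analysis plan.

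**Conclusion.** As written, the method is wrong for ORR. This rests on the article's own text and needs no assumption: Kaplan-Meier is assigned to an endpoint that the article defines as a response rate.

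The numerical consequence is conditional. If non-responders are censored at progression or withdrawal, the estimate equals or exceeds the proportion responding: 27% to 58% against 20% in the two-responder sequences with responses at weeks 6 and 12, and about 3 to 9 points on average under the simulated rates. All of these rest on assumed event patterns, since the article gives no response or progression rates. A reader might conclude that the reported ORR will certainly be inflated, or by nearly 40 points. Neither follows.

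The point should be fixed, but it is not critical. ORR is one of several secondary endpoints in an exploratory, single-arm study of about 10 patients whose primary objective is safety, and the article states no hypothesis test or decision threshold for ORR.

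**What to change.** Replace the single sentence on method with two statements:

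1. Kaplan-Meier is used for PFS, TTP and OS.
2. ORR is the number of responders divided by all treated patients, with non-evaluable patients counted as non-responders, reported with a Clopper-Pearson 95% confidence interval.

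This brings the ORR analysis into line with the all-treated population already stated. It costs two sentences and needs no new data, no extra patients and no change to the assessment schedule.
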